**Severity of OHSS**	
Mild OHSS	Abdominal bloating Mild abdominal pain Ovarian size is usually below 8 cm
Moderate OHSS	Patients do not meet the criteria of severe (described below) and have fluid accumulation in abdomen (ascites), confirmed by ultrasound scan. The following symptoms may also be present: Moderate abdominal pain Increased ovarian size of usually 8–12 cm Nausea with or without vomiting Some degree of clinical judgement may be needed to confirm the diagnosis of moderate OHSS.
Severe OHSS	Patients have fluid accumulation in abdomen (clinical ascites/clinically detectable fluids), confirmed by ultrasound, with or without hydrothorax The main distinguishing features are any of the following: Low urine output (oliguria) (<300 mL/day or <30 mL/hour) Haematocrit>0.45, (confirmed via full blood count (FBC) test) Ovarian size>12 cm.
Critical OHSS	Clinically obvious ascites, with one of the following features: the patient has a tense ascites or a large hydrothorax Haematocrit level >0.55 (confirmed via FBC test)* A white cell count of over 25 000 /mL (confirmed via FBC test) Anuria (very little/no urine) (<100 mL/day) Thromboembolism Acute respiratory distress syndrome

*Haematocrit level is the most important measurement.

hCG, human chorionic gonadotropin; OHSS, ovarian hyperstimulation syndrome; RCOG, Royal College of Obstetricians and Gynaecologists.

Clinical practice usually involves monitoring the patient until the condition becomes severe, when the patient is admitted to hospital, as recommended by the RCOG guideline.^1^ Inpatient management often includes drainage of ascitic fluid (paracentesis) which can result in a significant improvement of the condition and in renal blood fluid, urine output and reversal of the haematological abnormalities.^4–6^ Complications such as venous thromboembolism can have long-term health problems lasting well beyond the length of the pregnancy.

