Establish whether OP prevents the escalation of OHSS severity.Establish whether OP reduces the time taken for OHSS symptoms to resolve.Establish the safety of OP as an active intervention for moderate or severe OHSS.Explore whether OP would improve patient satisfaction and quality of life.Establish whether OP is cost-effective by examining healthcare resource use and patient costs.Facilitate the feasibility of conducting the RCT by identifying problems with the conduct of the RCT during an internal pilot.

Pretrial development work involved qualitative interviews with clinicians and patients exploring the feasibility and acceptability of earlier active management protocols. These results fed into a consensus event to confirm the treatment protocol used in the RCT. We also undertook a comprehensive audit of proposed RCT centres to inform the parameters used to design the RCT.

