### Intervention and control

Following randomisation, women in the intervention arm will have OP performed in the outpatient setting as soon as clinically possible. Sites will follow their own local procedures for conducting paracentesis either abdominally or vaginally by a suitably trained doctor, advanced nurse practitioner or radiologist in the fertility, gynaecology or radiology unit and while the trial does not dictate how to perform the intervention, guidance will be offered.

If rehydration is required via intravenous methods, this will be at the discretion of the attending clinician. If a large volume of fluid is removed, then intravenous colloid therapy should be considered. If this administration of fluid results in overnight inpatient hospitalisation it will not be viewed as meeting the trials primary outcome relating to hospitalisation. Some patients may require multiple drainage which can be performed if the participant has a reaccumulation of ascites.

Women in the UC group will not have the paracentesis performed in an OP setting and will be monitored by their clinical team as per UC. If UC at the site involves administering paracentesis on an outpatient basis for treatment of OHSS then the site will be requested to stop routinely providing this for participants in the UC arm.

Both groups of women will be provided with access to a diary (either in paper format or sent electronically using Research Electronic Data Capture (REDCap)^18^ hosted at The University of Sheffield for the purpose of daily self-report of weight, abdominal girth, diarrhoea, vomiting, pain, shortness of breath, fluid input and urine output. This information will be used by the clinical team in the intervention arm on a daily basis to inform further management and whether to perform further OP. The UC group will also perform daily self-monitoring, but these data will be sent directly to CTRU for input into the database and will not be available to be reviewed by site staff.

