OHSS-related hospitalisation for at least 24 hours within 28 days of randomisation.

Secondary outcomes:

Need for OHSS-related hospitalisation within 28 days—independent blinded central assessment.Time to resolution of OHSS assessed within 28 days of randomisation.Progression of OHSS severity within 28 days of randomisation.Cumulative length of OHSS-related hospitalisation.Live birth, pregnancy outcomes, neonatal death and serious adverse events (SAEs) including congenital abnormalities in the new-born within 13.5 months of randomisation.The occurrence of thrombosis, embolism and significant infections requiring antibiotic treatment or hospitalisation within 90 days of randomisation.AEs within 28 days of randomisation.Patient satisfaction assessed using the Client Satisfaction Questionnaire 8^19^ based on total scores at 28 days postrandomisation.EQ-5D-5L participant quality of life daily and at 28 days postrandomisation.Health resource use and patient costs at 28 days postrandomisation.

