### Statistical analysis

Detailed of all analysis will be described in an open-access and prespecified SAP to be developed and signed off before accessing unblinded data.

The primary analysis will be an intention to treat, including all eligible participants randomised with informed consent. Baseline data will be summarised at the interim and final analyses by treatment group. The absolute difference in hospitalisation rates between arms is the primary summary measure of the treatment effect. RR and OR (estimated using a simple logistic regression model) will also be presented. At an interim analysis, the unadjusted difference in hospitalisation rates between arms will be calculated to inform the interim decision on whether to stop early for futility. For sensitivity analysis, a mixed effects logistic regression model adjusted for stratification factors (site as a random effect and OHSS severity as a fixed effect) and adjusted difference in hospitalisation rates will be obtained using the delta method via margins.^21^ For the final analysis of the primary outcome, the unadjusted difference in hospitalisation rates with CI obtained via normal approximation will be reported as well as the p value from a χ^2^ test. Stagewise ordering will be used for sensitivity analysis to obtain the median unbiased estimate of the difference in hospitalisation rates between arms with the associated 95% CI to be presented alongside the maximum likelihood estimate if the trial progressed beyond interim analysis. The details of additional sensitivity analyses to be performed adjusting for baseline covariates are found in the SAP. Reporting will adhere to the adaptive designs CONSORT (Consolidated Standards of Reporting Trials) Extension guidance.^22^

For progression of OHSS severity, a mixed effects logistic regression model adjusted for stratification factors (site as a random effect and OHSS severity as a fixed effect) will be used and an adjusted difference in hospitalisation rates will be obtained using the delta method via margins.^21^ Treatment effects will be presented as adjusted OR, adjusted risk difference and adjusted relative risk/RR with 95% CIs.

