For time to resolution of OHSS assessed within 28 days postrandomisation, Kaplan-Meier curves will be used to visualise the resolution curves between treatment arms and differences qualified using a log-rank test. Median time to resolution by treatment arm with 95% CI will be calculated and reported as summary measures of within-group effects. Participants who fail to achieve resolution of symptoms within 28 days postrandomisation will be censored. Sensitivity analysis and alternative approaches when the proportional hazard assumption is not met will be detailed in the SAP.

For cumulative length of OHSS hospital stay, bootstrapping resampling procedure (accounting for stratification) will be used to obtain the median difference with 95% CI and associated p value. For patient satisfaction at 28 days, a total satisfaction score will be analysed using a mixed effects linear regression model adjusted for site (as a random effect) and OHSS severity (as a fixed effect), and the adjusted mean difference between treatment arms with 95% CI and associated p value will be presented.

Analysis of safety outcomes (eg, AEs and SAEs) will be based on descriptive statistics using the safety analysis population defined based on treatment-as-received population. Details of additional analysis accounting for repeated events and differential follow-up is found in the SAP.

Subgroup analyse will be performed to explore whether there is heterogeneity in treatment effect on the primary outcome across the following prespecified subgroups:

Baseline severity of OHSS (moderate or severe).Whether a participant is taking a preventative drug at randomisation (yes or no).Whether the participant has early or late OHSS at randomisation.Whether the OP procedure was done vaginally or abdominally. For participants who received multiple procedure (which may happen in few cases), this classification will be based on the first performed procedure.

A mixed effects logistic regression model that includes an interaction effect between preplanned subgroup and treatment group adjusted for site (as a random effect) and severity of OHSS (as a fixed effect) only if it is not a subgroup factor of interest will be used.

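### The only safety population named is treatment received, with receipt undefined; because drainage can follow a woman's course after randomisation, AEs and SAEs should be tabulated by randomised arm

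*Protocol article*

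**What the plan says.** Statistical analysis section: safety outcomes, with AEs and SAEs as examples, are described "using the safety analysis population defined based on treatment-as-received population". No other safety population is named. What the section leaves to the SAP on safety is put this way: "Details of additional analysis accounting for repeated events and differential follow-up is found in the SAP". Neither item is an analysis by randomised arm. Intention to treat is stated for the primary analysis: "The primary analysis will be an intention to treat, including all eligible participants randomised with informed consent".

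Safety is a secondary objective (Introduction): "Establish the safety of OP as an active intervention for moderate or severe OHSS". The Outcomes section separately lists "The occurrence of thrombosis, embolism and significant infections requiring antibiotic treatment or hospitalisation within 90 days of randomisation".

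Three statements bear on who receives paracentesis:

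- Intervention and control: "women in the intervention arm will have OP performed in the outpatient setting as soon as clinically possible".
- Same section: UC women are not to have outpatient drainage, and where a site already offers it as usual care, "then the site will be requested to stop routinely providing this for participants in the UC arm".
- Introduction, after Table 1, on current practice once a woman has been admitted: "Inpatient management often includes drainage of ascitic fluid (paracentesis").

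The article also foresees that study treatment may stop by choice or for clinical need, and says that women who withdraw from the intervention stay in follow-up.

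**The concern.** An as-received safety set is least troublesome when few women depart from their assigned treatment, or when departure has little to do with prognosis. Here the link to prognosis is built in. The control strategy is to monitor, admit if the condition becomes severe, and often drain then, so the UC women most likely to be drained are those who have worsened. Table 1 lists thromboembolism as a feature of critical disease, so worsening also goes with the events of interest. In the OP arm there is a gap between randomisation and first drainage, in which a woman may worsen and be admitted, improve, or withdraw.

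If such women change group, their events go with them. Worsening UC women counted as treated make OP look more harmful. So do improving OP women counted as untreated. Worsening OP women counted as untreated make OP look safer. The randomised comparison is lost, and only it compares early outpatient drainage fairly with waiting. Calling the analysis descriptive does not remove the problem, because readers will compare the two columns.

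**Working it through.** **Arm sizes.** The article gives no safety figure, so the only figure to reproduce is the sample size. For 41% vs 21%, one-sided 2.5% and 90% power, the pooled two-proportion formula gives 111 per arm. The article states about 112, at which power is 90.4%. I use 112 per arm.

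**Does the text settle who counts as treated?** The intervention is described as paracentesis in the outpatient setting, which suggests that inpatient drainage in UC should not count. The safety sentence does not say so, however, and the Table 2 row on intervention delivery (ascites volume and number of procedures) is filled from medical notes during hospitalisation without being limited to the OP arm. The natural reading leaves admitted and drained UC women in UC, but the other reading is open.

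**Scenario A: no true effect.** Assumptions, none from the documents except that 41% is borrowed from the planned UC admission rate:

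- w = 41% of women worsen in each arm.
- SAE risk is r0 if not worsening and r1 if worsening.
- c = share of worsening UC women drained and counted as treated.
- m = share of non-worsening OP women never drained and counted as UC.

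Treated group: n = 112[1 − (1−w)m] + 112wc; events = 112[w·r1 + (1−w)(1−m)r0] + 112wc·r1. The UC group is the remainder of 224 women and of all events.

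Example, r0 = 3%, r1 = 15%, c = 25%, m = 10%: treated 10.39/116.9 = 8.9%; UC 7.35/107.1 = 6.9%; risk ratio 1.30. By randomised arm both are 7.92%, ratio 1.00.

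| c | m | RR at 5%/10% | RR at 3%/15% | RR at 2%/20% |
|---|---|---|---|---|
| 0 | 0 | 1.00 | 1.00 | 1.00 |
| 10% | 0 | 1.03 | 1.08 | 1.10 |
| 0 | 10% | 1.03 | 1.08 | 1.10 |
| 10% | 10% | 1.07 | 1.16 | 1.20 |
| 25% | 10% | 1.13 | 1.30 | 1.39 |
| 50% | 10% | 1.24 | 1.61 | 1.84 |

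Opposite direction: suppose 10% of worsening OP women (0.10 × 45.92 = 4.59) are admitted before drainage and counted as UC. At 3%/15% there are 112 × 0.0792 = 8.87 events per arm, of which 4.59 × 0.15 = 0.69 move. OP is 8.18/107.4 = 7.6%, UC is 9.56/116.6 = 8.2%, ratio 0.93.

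**Scenario B: OP truly beneficial.** Assume serious complications occur only in admitted women, at 5%. Admitted: UC 0.41 × 112 = 45.92; OP 0.21 × 112 = 23.52. Events: 2.30 and 1.18. Let d be the share of admitted UC women drained **and counted as treated**.

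Treated risk = (1.176 + 2.296d)/(112 + 45.92d); UC risk = 2.296(1−d)/(112 − 45.92d).

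| d | Treated | UC | RR |
|---|---|---|---|
| 0 (as randomised) | 1.05% | 2.05% | 0.51 |
| 25% | 1.42% | 1.71% | 0.83 |
| 50% | 1.72% | 1.29% | 1.34 |
| 75% | 1.98% | 0.74% | 2.67 |

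Break-even: set (0.21 + 0.41d)(1 − 0.41d) equal to 0.41(1−d)(1 + 0.41d). The squared terms cancel, leaving 0.5658d = 0.20, so d = 35%, about 16 of 46 admitted UC women. The 5% cancels as well. It sets the level of risk but not the break-even point.

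**The case against.** The strongest reply is that the article defines the intervention as outpatient paracentesis and treats inpatient drainage as part of current care. On that reading an admitted and drained UC woman has received usual care, d is zero, and Scenario B stays at 1.05% vs 2.05%. This stands as the more natural reading, and it removes the largest route of distortion. It does not settle the matter, because the safety sentence leaves receipt undefined.

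The remaining routes are probably small. First drainage is meant to follow randomisation promptly, and women already needing admission are excluded. UC women are not meant to have outpatient drainage, and the softer wording about routine provision applies only to sites where it is already usual care. These routes also pull in different directions. This stands too: with only 10% of non-worsening OP women undrained, Scenario A gives ratios of 1.03 to 1.10.

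An as-received set is also a common convention, serves to attribute harm to the procedure undergone, and is purely descriptive here. That is a good reason to keep it, but not to have it without a by-arm counterpart when the trial compares two strategies.

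Finally, this is a condensed article, and the SAP, which is not shown, may add by-arm tables or define receipt. That is possible, but the article itself fixes the safety population, and what it describes as deferred is something else.

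**Conclusion.** The point holds in a limited form. As-received is the only safety grouping the article names, receipt is not defined, and receipt can depend on the course after randomisation. The AE and SAE comparison can therefore be distorted in either direction. The size cannot be learned from the documents, which give no crossover or SAE rate. Over the assumed ranges the false risk ratio runs from 1.03 to 1.84 when no true effect exists, and to about 0.93 in the opposite-direction example. With no crossover it is zero. The primary analysis is not affected.

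Two stronger readings are tempting and are not supported:

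- A reader might infer that the safety contrast will change sign. In Scenario B that needs inpatient drainage to count as the intervention, against the article's own description of it, and about 35% or more of admitted UC women to be drained. At 25% there is attenuation but no reversal, and the whole contrast rests on about 3.5 expected events (2.30 + 1.18).
- A reader might infer that thrombosis, embolism, infection and newborn outcomes are all analysed as received. The sentence gives only AEs and SAEs as examples; the others are listed as separate secondary outcomes, and their population is not stated.

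**What to change.** In the protocol and SAP, before unblinded data are accessed:

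1. Make the main safety tables for AEs and SAEs by randomised arm, including all randomised women. Do the same for thrombosis/embolism and infection if they fall under the same rule, and say whether they do.
2. Keep treatment received as a supportive table. For this table, define receipt of OP as at least one outpatient procedure, so that inpatient drainage in UC does not move a woman between groups.
3. List procedure-related events among women who had OP, which answers the separate question of harm from the procedure itself.

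The cost is a sentence or two of text and one extra set of descriptive tables. No new data should be needed: women who withdraw from the intervention are still followed, and Table 2 already records the procedures.

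### The vaginal-or-abdominal subgroup is fixed after randomisation and has no value in the usual care arm, so the planned route-by-treatment interaction cannot be estimated

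*Protocol article*

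**What the plan says.** In the protocol article, under Statistical analysis, the subgroup analyses are meant to "explore whether there is heterogeneity in treatment effect on the primary outcome across the following prespecified subgroups". Four factors are listed: baseline severity, use of a preventative drug at randomisation, early or late OHSS at randomisation, and "Whether the OP procedure was done vaginally or abdominally". For women with more than one drainage, "this classification will be based on the first performed procedure". The model then applies to the whole list, with no exception for route: "A mixed effects logistic regression model that includes an interaction effect between preplanned subgroup and treatment group", adjusted for site as a random effect and for severity unless severity is itself the subgroup.

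The section Intervention and control says when and to whom the procedure happens: "Following randomisation, women in the intervention arm will have OP performed in the outpatient setting as soon as clinically possible". For the comparator, "Women in the UC group will not have the paracentesis performed in an OP setting". It also says how route is chosen: "Sites will follow their own local procedures for conducting paracentesis either abdominally or vaginally". Route is neither randomised nor a stratification factor. Under Randomisation and concealment, the stratifiers are site and OHSS severity.

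**The concern.** A subgroup-by-treatment interaction asks whether the treatment effect differs between two kinds of participant. Each kind must therefore exist in both arms, and membership should not depend on what happened after allocation. Severity, preventative drug use and early or late OHSS meet both conditions. Route of the procedure performed meets neither: it describes how the intervention was delivered, not the woman who was randomised.

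Route varies with local practice, so readers will want to know whether it matters. As written, the prespecified analysis cannot tell them. The analyst would have to improvise a comparator or accept whatever the software returns after dropping a term, and the benefit of prespecification would be lost.

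**Working it through.** **Inputs.** The article gives no figure for this analysis. The only number needed is the planned 112 per arm (Sample size and interim analyses), and it reproduces. With rates of 41% and 21%, one-sided alpha of 2.5%, 90% power and the pooled two-proportion formula:

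n = [1.960 × √(2 × 0.31 × 0.69) + 1.282 × √(0.41 × 0.59 + 0.21 × 0.79)]² / 0.20² ≈ 110.3, so 111 per arm, against the stated 112.

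This is context only; the argument below holds for any sample size.

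**What the interaction needs.** Let V and A be vaginal and abdominal, and p the probability of the primary outcome. On the logit scale the interaction is

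[logit p(OP,V) − logit p(UC,V)] − [logit p(OP,A) − logit p(UC,A)].

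The OP arm supplies p(OP,V) and p(OP,A). Nothing supplies p(UC,V) or p(UC,A), because UC women have no OP procedure to classify. The data give only logit p(OP,V) − logit p(OP,A). That equals the interaction only if UC risk is assumed to be the same for women who would have been drained by either route. The data cannot test this assumption, and since route follows local practice, there is no reason to take it for granted.

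**The same point in the design matrix.** Take fixed effects for intercept, treatment T (OP = 1), route R, T × R and severity: five columns. A 56/56 split of routes within OP is assumed for illustration; the result holds for any split in which both routes occur.

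| How UC women are handled | Dependence among columns | Rank |
|---|---|---|
| All coded R = 0 | T × R = R | 4 of 5 |
| All coded R = 1 | T × R = R − (1 − T) | 4 of 5 |
| Route missing, rows drop out | T = intercept and T × R = R | 3 of 5 |
| Three-level factor: UC, OP-vaginal, OP-abdominal | none, but no interaction term | 4 of 4 |
| Route defined by site for both arms | none | 5 of 5 |

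In the first three rows the interaction has no estimate of its own. The random site effect does not help while route remains a participant-level variable taken from the procedure performed.

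**Women in the OP arm without a procedure.** They have no first procedure and so no route. Leaving them out departs from the intention-to-treat basis stated for the primary analysis.

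**The case against.** **A SAP is promised, and the subgroups are exploratory.** Both are true, and both limit the importance of the point. But the article itself fixes the subgroup definition and the model. This is a stated rule that cannot work, not detail left for later.

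**Something can be fitted.** If UC women are coded to one level, software will usually drop the redundant column and leave OP-vaginal and OP-abdominal, each against all of UC. That three-level model has full rank, so it would be too strong to say that nothing at all can be reported about route. It is not the planned interaction, however. It compares non-randomised parts of one arm with the whole of the other, and the choice of part follows local site practice.

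**Some UC women may acquire a route.** Sites that already offer outpatient paracentesis are only asked to stop providing it routinely in the UC arm, so crossover is possible. The Introduction also notes that inpatient care often includes drainage. Such routes would be few, would arise after randomisation, and may be selected by deterioration; they do not rescue the interaction.

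**A stronger reading.** A reader might infer that UC women drained in hospital would serve as the comparator, that nearly all would have the primary outcome, and that the model would show a spuriously large benefit for both routes. The documents do not support this. The subgroup refers to the OP procedure, and nowhere are UC inpatients given a route. Even if they were, the primary outcome requires an OHSS-related stay of at least 24 hours, so a shorter admission for drainage would not be an event. No size of bias should be attached to the point.

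**Conclusion.** The point holds as a matter of structure. The route-by-treatment interaction prescribed in the article is not identified, because route is a post-randomisation attribute with no value by design for the 112 planned UC women, and none for OP women who are never drained. Any contrast by route actually used is observational and confounded with site.

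This rests on two things the article states: route is taken from the first procedure performed, and UC women do not have OP. It needs no assumption about event rates or about how the routes divide.

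The reach is limited to one of four exploratory subgroup analyses. The other three factors are defined at baseline in both arms. The primary analysis, the interim futility rule and the sample size are unaffected. The plan should be corrected, but the trial's main conclusion does not depend on it.

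**What to change.** 1. Remove route from the list of factors to which the interaction model applies. Report the route actually used, by first procedure, as an exploratory description within the OP arm only, and state the number of OP women who had no procedure.
2. If effect modification by route is wanted, define it by each site's usual paracentesis route. Take this from the site's local procedure and lock it in the SAP before unblinded data are accessed. Every woman in both arms then has a value, and because randomisation is stratified by site, the comparison within each route group remains randomised.

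Recruitment began in June 2022, so for open sites the usual route has to be taken from existing local procedures; it can no longer be recorded everywhere before the first randomisation.

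The cost is one site-level field and a short passage in the SAP. There are two downsides to the second step. Sites that use both routes need a category of their own. With about 20 sites, the contrast will be imprecise and confounded with other differences between sites, and should be reported with that caution. If that is judged not worth having, the first step alone is enough.
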